## Abstract

Despite advances in the understanding of cognitive dysfunction among people with epilepsy (PWE), evidence for cognitive rehabilitation in epilepsy (CoRE) remains scarce. We present the protocol of a randomized waitlist-controlled trial (ClinicalTrials.gov ID NCT05934786) of a psychological-behavioral intervention aiming to ameliorate quality of life as well as cognitive functioning in a mixed PWE sample. The study is set at Vilnius University Hospital Santaros Klinikos and will offer adult PWE six individual and two group sessions led by a certified psychologist and directed toward improving memory, attention, self-regulation, mood and quality of life. The trial is expected to address major gaps in the literature by providing novel evidence on the effectiveness of CoRE in patients with genetic generalized epilepsies, the importance of epilepsy-specific factors for the response to CoRE, the impact of CoRE on long-term memory as well as its maintenance effects.

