## Introduction

1.

Epilepsy is a multifaceted chronic neurologic disorder that occurs in every hundred individuals and directly affects patients’ cognition, quality of life as well as professional and societal activities (1). Because of premature mortality, mental health and socioeconomic implications of this disorder, it is now also recognized as a global public health priority by the World Health Organization (2). Cognitive dysfunction is a major burden for people with epilepsy (PWE) as epilepsy limits their ability to remember, learn, focus, and think. It has been shown that a third of newly diagnosed PWE have subjective cognitive complaints, and up to one half perform worse than controls during objective neuropsychological evaluation (3). Epilepsy can affect various cognitive domains, such as memory or attention, with a possible increase in the level of impairment over time (4). While the problem of prevalent cognitive dysfunction is well-known and may have significant impact on quality of life and social functioning in epilepsy, studies investigating the feasibility and efficacy of cognitive rehabilitation in epilepsy (CoRE) are rare: just nine group studies were identified in the most recent systematic review (5). Importantly, most were of only moderate quality. The lack of new studies of CoRE is seen as a significant shortcoming of modern epileptology: this neglect is thought to stem from a lack in resources and a historical focus on seizure control rather than cognitive outcomes in the clinical setting (6).

We aim to conduct a novel randomized waitlist-controlled cross-over trial of an original CoRE program, assess its overall efficacity and determine factors associated with a better response to this intervention. The main hypothesis of the trial is that a combined individual and group CoRE program is effective in improving quality of life and verbal as well as visual memory in PWE.

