### Sample size and statistical analysis

2.7.

The target sample size of the study was calculated for a between-group interaction of a two-way repeated measures analysis of variance (ANOVA) with *f* = 0.40, *α* = 0.05, *β* = 0.95, two groups (early and late intervention), three measurement points, and 0.5 correlation between repeated measures. The resulting sample size of *n* = 58 (G*Power 3.1.9.7) was increased by 20% to *n* = 70 to account for dropouts (including the possibility of patient referral to presurgical evaluation if needed according to principles of best medical practice) and corresponded well to the mean sample size and attrition rates in previous trials (5). This sample size is deemed achievable as the trial will be conducted in a large university hospital covering tertiary epilepsy care services for approximately 1.4 million of inhabitants and include a group of PWE composed of patients with both TLE and GGE.

The efficacy of the intervention will be defined as statistically significant improvement on one of the primary outcomes (quality of life or delayed memory), tested with a repeated-measures between-factors analysis of variance (ANOVA) in the EIG as compared to the LIG. For secondary analyses, dynamic changes of other outcome measures will be tested, respectively, by using ANOVA or ANCOVA. The association between demographic and clinical variables with study endpoints will be conducted by means of linear and ordinal regression modeling. Subgroup analyses are planned to be conducted based on sex, education status, professional status, epilepsy type, laterality and lesionality. In case of missing data, multiple imputation will be used in sensitivity analysis.

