## Discussion

3.

This protocol describes a planned randomized waitlist-control trial of CoRE in epilepsy. The study was designed to address major research gaps identified through recent systematic literature reviews in this field, as discussed below (5, 6, 23).

First, the study will include patients with genetic generalized epilepsy (GGE). Most trials examined CoRE by including patients with temporal lobe epilepsy (TLE), often in the context of presurgical evaluation (5, 24–26). As epilepsy surgery is not indicated in GGE, these patients are less frequently tested for neuropsychological deficits and have long been thought to have nearly normal cognitive functions. However, recent studies show frequent cognitive dysfunction in GGE as well (27). Their inclusion is expected to help define the efficacy of CoRE when there is no indication that seizure onset is focal (as is expected in both lesional or non-lesional TLE). While the inclusion of patients with GGE makes the study sample more heterogeneous than if only patients with TLE were enrolled, we believe there will remain opportunities to detect the effects of CoRE on different types of epilepsy through subgroup analysis in case of a large effect size.

Second, we are planning to investigate epilepsy-associated factors in response to cognitive rehabilitation beyond seizure laterality. Only two of the previous trials examined the impact of background patient epilepsy-related variables (e.g., seizure frequency, polytherapy, epilepsy onset time) on the efficacy of CoRE (5, 26, 28). This information will be gathered through standardized patient forms and included in secondary analyses.

Our project also includes novel measures of cognitive assessment. Baseline and follow-up assessments will consist of both traditional and experimental neuropsychological tools. While traditional instruments will ensure the comparability of the results with previous studies, novel tools will be essential to address the need to train and test ecologically valid everyday cognitive functions. We selected to test memory of a week’s schedule of daily activities – the task is expected to depend on attention, short-term visual and verbal memory as well as associative learning and transfer effects. Furthermore, we envision evaluating patients for accelerated long-term forgetting – to the best of our knowledge, the effects of CoRE on long-term memory deficits have not been investigated in earlier studies (29).

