## Limitations

4.

Despite the advantages of the planned study mentioned above, some of its limitations should be considered as well. First, the study will be of a single-country and single-center design, imposing boundaries on the sample size, generalizability of the study findings as well as the application of the intervention in different socioeconomic and cultural backgrounds. Second, the PWE group is expected to be heterogeneous in epilepsy type. This limitation will be addressed through subgroup and adjusted analyses. Third, the intervention will be focused on improving cognitive strategies rather than directly training selected cognitive domains. This may decrease the perceived effectiveness of the CoRE program on objective cognitive functioning as the effects of near transfer in such rehabilitation remain unknown. Finally, despite a longer follow-up than in other studies, the understanding of any emerging maintenance effects will remain limited to a relatively short period of 4 months.

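### The regression planned to find who responds better to CoRE estimates prognosis rather than a difference in treatment effect, and no treatment-by-factor interaction is named

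*Protocol article*

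**What the plan says.** The protocol article states the aim several times, each time in terms of response to the intervention. The Introduction wants to "determine factors associated with a better response to this intervention". The Abstract promises evidence on "the importance of epilepsy-specific factors for the response to CoRE". Section 3 (Discussion) says "we are planning to investigate epilepsy-associated factors in response to cognitive rehabilitation beyond seizure laterality", and section 6 (Conclusion) again promises information on what determines the programme's effects.

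Section 2.7 gives two analyses that could serve this aim. The first is a regression: "The association between demographic and clinical variables with study endpoints will be conducted by means of linear and ordinal regression modeling". The second is a list of six factors: "Subgroup analyses are planned to be conducted based on sex, education status, professional status, epilepsy type, laterality and lesionality". The article does not say how the subgroups will be analysed. Section 3 gives the nearest indication, expecting to "detect the effects of CoRE on different types of epilepsy through subgroup analysis in case of a large effect size". Section 4 says of the mixed epilepsy types: "This limitation will be addressed through subgroup and adjusted analyses".

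No test of whether the treatment effect varies with a patient factor is named anywhere. The word interaction occurs only in the sample-size sentence, where it refers to the group comparison in the repeated-measures ANOVA.

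**The concern.** A factor can relate to an endpoint in two ways. It can be prognostic: patients with it score higher or lower whether or not they are treated. Or it can modify the effect: the difference between the early intervention group (EIG) and the late intervention group (LIG) is larger in patients with it. The aim concerns the second, while a regression of endpoints on patient variables estimates the first.

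The subgroup analyses do not clearly close the gap. If they test for an effect within temporal lobe epilepsy (TLE) and within genetic generalized epilepsy (GGE), the two p-values can easily fall on opposite sides of 0.05 although the true effects are equal.

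Determinants of response and evidence in GGE are two of the contributions by which the article justifies the trial. If section 2.7 is followed literally, prognostic factors could be read as predictors of response and real modifiers could be missed.

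**Working it through.** **The plan's own figure.** Inputs from section 2.7: f = 0.40, α = 0.05, power 0.95 (printed as β), two groups, m = 3 measurements, ρ = 0.5. For the between-group test, λ = f²·N·m / (1 + (m − 1)ρ) = 0.16 × 3 / 2 × N = 0.24N, with 1 and N − 2 degrees of freedom. At N = 58, λ = 13.92 and power is 0.956; at N = 56 it is 0.9495. So 58 reproduces, and 58 × 1.2 = 69.6, rounded to 70. This size serves the overall group effect only. With two equal groups, f = 0.40 is d = 0.8.

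**What the regression detects.** Simulation with N = 58, one follow-up score with residual SD 1, a binary factor x split 50:50, arm g, and 3,000 runs per scenario:

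y = 0.8·g + a·(x − 0.5) + b·g·(x − 0.5) + error

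The pooled regression contains arm and factor. The interaction model adds their product.

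| Truth | Regression, both arms | Regression, EIG only | Interaction test |
|---|---|---|---|
| Prognostic only (a = 0.8, b = 0) | 85% | 54% | 4.6% |
| Modifier, no average association (a = −0.4, b = 0.8) | 4.8% | 17% | 32% |

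In the first row the treatment effect is the same for everyone, yet the regression is usually significant. In the second row the effect differs by 0.8 SD, and the pooled regression rejects no more often than its 5% error rate.

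**What side-by-side subgroup tests show.** With no modification and a true effect of 0.8 SD in both halves, one test was significant and the other not in about 50% of runs (single follow-up). On the plan's three-visit model, a subgroup of 29 has power p = 0.72, so the chance of disagreement is 2p(1 − p) = 2 × 0.72 × 0.28 = 0.40. With 35 per subgroup, p = 0.803 and the chance is 2 × 0.803 × 0.197 = 0.32.

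**Power of the right test.** For a binary factor with share q and equal arms, the four cells hold Nq/2, Nq/2, N(1 − q)/2 and N(1 − q)/2 patients. SE = SD × √(sum of 1/cell size), referred to a noncentral t with N − 4 degrees of freedom. SD = 1 for a single visit, or √((1 + 2 × 0.5)/3) = 0.816 for the mean of three visits. Example at N = 58 and q = 0.5: cells of 14.5, √(4/14.5) = 0.525, SE = 0.816 × 0.525 = 0.429, 0.8/0.429 = 1.87, power 45%.

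| Difference in effect 0.8 SD | Mean of three visits | Single visit |
|---|---|---|
| N = 58, 50:50 | 45% | 32% |
| N = 58, 30:70 | 39% | 28% |
| N = 70, 50:50 | 52% | 38% |
| N = 70, 30:70 | 46% | 33% |

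For a difference of 0.4 SD, power is 10–17% over the same range. For 80% power at 0.8 SD, the total N would have to be 134–200 (50:50) or 158–236 (30:70). The factor splits are assumptions; the article gives none.

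**The case against.** The strongest reply is that section 2.7 is a short part of a condensed article. Model terms and subgroup methods normally sit in a full protocol or analysis plan, and nothing in the text forbids an interaction term. This stands for the subgroup analyses, whose method is simply not given. It does not dispose of the regression, because there the article names an analysis, and what that analysis estimates differs from the aim.

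A second reply is that these are secondary analyses. Efficacy is decided on the primary outcomes alone, section 3 makes subgroup detection conditional on a large effect, and section 4 lists heterogeneity as a limitation. This is correct and limits the consequences: no efficacy claim depends on the point. The condition protects little, however, since d = 0.8 is already the effect for which the whole sample was sized.

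A third reply is that an endpoint could be taken as change from baseline, which would remove a stable prognostic difference. The 85% figure does apply to the score itself. But a slope pooled over both arms still mixes treated and untreated patients, and a slope in the EIG alone cannot separate response from retest gain. Section 2.5 itself prefers comparing the groups to comparing with baseline because of learning effects.

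Finally, an interaction test in 58 to 70 patients is weak. That is true and belongs in the plan as a caveat. It does not make the association regression a substitute.

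**Conclusion.** The regression in section 2.7 is aimed at prognosis, while the Abstract, Introduction, Discussion and Conclusion speak of response to the intervention, and the article names no treatment-by-factor interaction. Under the simulated conditions (N = 58, treatment effect 0.8 SD, binary factor split 50:50, one follow-up), the stated regression picks out a non-modifier in 85% of runs and a true 0.8 SD modifier without average association in about 5%. If subgroups are judged by separate p-values, they disagree by chance in roughly 32–50% of trials when the effect is really the same.

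A reader might infer more: that neither planned analysis can test the aim, so that it will go unanswered. The documents do not support this. The article does not say that subgroups will be tested separately; section 3 only leans that way, and an analysis plan not shown may specify interactions. A reader might also multiply factors, levels and outcomes into a near-certain false positive. The article gives neither the levels of each factor nor the outcomes to be tested by subgroup, and such tests on the same patients are not independent, so no such figure can be derived.

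**What to change.** For the response aim, add treatment-by-factor (by-time) interaction terms to the planned between-group model, using both arms. Restrict them to a short pre-specified list that includes epilepsy type, which is already a minimization factor in section 2.6. Report each interaction estimate with its confidence interval, and present within-subgroup effects as descriptive only. Fit laterality and lesionality only in the patients to whom they apply. Keep the association regression, labelled as an analysis of prognosis.

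This changes wording and model terms; it needs no further patients, visits or data. The cost is candour about precision. At 28–52% power for a difference as large as the planned main effect, the interaction analyses must be labelled exploratory, a non-significant term must not be read as equal effects, and fewer subgroup claims can be made.

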### Participant recruitment, allocation, and timeline

2.6.

Study participants will be invited to participate in the trial during routine outpatient visits at the epilepsy clinic. They will have either temporal lobe or genetic generalized epilepsy as confirmed by the epileptologist, according to previously collected clinical (e.g., seizure semiology, patient history), instrumental (e.g., electroencephalography, video-electroencephalography), genetic and imaging (e.g., 3T magnetic resonance imaging) data required to substantiate the diagnosis according to guidelines by the International League Against Epilepsy. After acceptance, each new participant will be randomly assigned to either the early intervention group (EIG) or the late intervention group (LIG) at the time of enrolment by using open-source software for minimization (WinPepi) based on sex, epilepsy type and seizure control. The randomization will be done, and participants assigned to one of the groups by the principal investigator. Outcome assessors and data analysts will be blinded to participant status by using concealed patient coding and instructing patients not to discuss their status during examination. The principal investigator, psychologists performing the intervention and participants themselves will not be blinded.

Both the EIG and the LIG will undergo neuropsychological assessment at three time points (Figure 2). The EIG will be tested at baseline, with two follow-ups four and sixteen weeks after the intervention which itself lasts for eight weeks. The LIG will be tested at the same time points while on waitlist. Participants assigned to the LIG will be offered the intervention after the second follow-up. Both groups will receive otherwise routine clinical care (i.e., according to individual needs and best medical practice) at the tertiary epilepsy clinic. Given the non-invasive nature of the CoRE intervention, no adverse effects are expected. Therefore, discontinuation of the intervention is expected to occur only in the case of participant dropout. Patient attrition will be minimized by thoroughly discussing the aims and procedures of the trial before enrolment as well as by accommodating to the patients’ availability and daily schedule for the weekly sessions.

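### As written, the primary repeated-measures ANOVA is by implication a complete-case analysis, and it can discard observed 4-week primary scores

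*Protocol article*

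**What the plan says.** The section on sample size and statistical analysis defines efficacy as a significant improvement on one of the primary outcomes, "tested with a repeated-measures between-factors analysis of variance (ANOVA) in the EIG as compared to the LIG". The sample size calculation behind that test assumes "three measurement points, and 0.5 correlation between repeated measures". The resulting 58 "was increased by 20% to *n* = 70 to account for dropouts". Missing data get one sentence: "In case of missing data, multiple imputation will be used in sensitivity analysis".

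On timing, the section on recruitment, allocation and timeline states: "The EIG will be tested at baseline, with two follow-ups four and sixteen weeks after the intervention". The late intervention group (LIG) is assessed at the same points while waiting. The trial registration table places all three primary outcomes (QOLIE-31-P, delayed verbal recall, delayed visual recall) at 4 weeks after the intervention.

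The article names no mixed model, no all-available-data rule and no analysis set.

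**The concern.** A classical repeated-measures ANOVA uses one row per participant with every visit filled in. If imputation is reserved for sensitivity analysis, nothing fills the gaps in the primary test, and anyone missing a visit drops out of it. The primary time point is the middle visit of three, so a participant can supply the primary measurement and still be excluded because a later visit was missed.

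Two things are at stake. Observed primary data are thrown away. And the comparison is no longer of the groups as randomised. Between baseline and the first follow-up only the early intervention group (EIG) has eight weeks of sessions and homework, and participants know their arm. Loss could therefore depend on arm and on how well the participant is doing, in which case the remaining completers are not comparable.

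**Working it through.** **1. Reproducing the plan's figure.** Inputs from the sample size section: f = 0.40, alpha = 0.05, power 0.95 (printed as β), two groups, m = 3 visits, correlation 0.5. For the between-factors test:

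lambda = f² × N × m / (1 + (m − 1) × rho) = 0.16 × N × 3 / 2 = 0.24N, with 1 and N − 2 degrees of freedom.

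- N = 56: lambda = 13.44, power 0.9495
- N = 58: lambda = 13.92, power 0.956
- N = 70: lambda = 16.80, power 0.981

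The smallest even N reaching 0.95 is 58, as stated. So 58 is the number of participants with all three visits that the test needs.

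**2. The dropout allowance.** 58 × 1.20 = 69.6, rounded to 70. Implied loss: (70 − 58) / 70 = 12/70 = 17.1%. Sizing on 58 and enrolling 70 fits an analysis to which the other 12 contribute nothing. Power is about 95.6% with 58 completers, so the issue is bias and discarded data, not power.

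**3. What the loss can do.** The article gives no missingness mechanism, so the following rests on assumptions that are not in it:

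- N = 70, 35 per arm (1:1 assumed), unit variance, correlation 0.5, no true effect.
- Everyone has baseline and 4-week scores; only week 16 can be missing.
- EIG: logit P(missing) = −1.8 − b × (4-week score). LIG: logit P(missing) = −1.8.
- b is the fall in log-odds of missing week 16 per SD of better 4-week score.

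Mean EIG minus LIG difference among participants with all three visits:

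| b | 4-week difference (SD) | Three-visit mean (SD) |
|---|---|---|
| 0 | 0 | 0 |
| 0.3 | +0.04 | +0.03 |
| 0.6 | +0.09 | +0.06 |
| 1.2 | +0.19 | +0.13 |

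The between-factors test compares three-visit means, so the last column is the bias in the named test; the middle column is the bias at the primary time point. At b = 1.2 about 83% are complete, with 19% missing in the EIG and 14% in the LIG, so fairly similar dropout rates would not reveal the problem. Type I error of the between-factors test rises from 5% to about 9 to 10%. Analysis of covariance on all observed 4-week scores gives 0.00 SD. This is expected, because no 4-week score is missing in this scenario.

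**4. Where the remedy stops working.** Take the same coefficients at b = 1.2, but let those participants miss both follow-ups. Baseline-adjusted analysis of the observed 4-week scores is then still biased by about +0.14 SD. A mixed model has no follow-up score from these participants either and would not remove that bias.

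**The case against.** **Complete-case analysis is inferred.** The article never mentions listwise deletion or completers, and a fuller protocol or analysis plan could define the analysis set. This stands as a caution about wording. It does not dispose of the point, because the article itself chooses the primary method and assigns imputation to sensitivity analysis. A plan consistent with both would keep the problem.

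**The illustration is one-sided.** It makes missingness depend on response in one arm only, and +0.19 SD needs a steep slope. This stands: at gentler slopes the bias is +0.04 to +0.09 SD, it is nil if loss is unrelated to outcome, and its direction in the real trial is unknown.

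**The planned imputation is a check.** In the scenario above it would bring back every observed 4-week score and expose a discrepancy. That is true, but the declared efficacy result would still be the complete-case one.

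**A stronger reading is tempting but unsupported.** A reader might infer that participants who stop sessions, or who are referred for presurgical evaluation, will go unassessed or be excluded. The sentence that "discontinuation of the intervention is expected to occur only in the case of participant dropout" follows a statement that no adverse effects are foreseen. It says that the investigators do not expect to stop the programme for harm. The sample was enlarged "to account for dropouts (including the possibility of patient referral to presurgical evaluation if needed according to principles of best medical practice", which justifies the number enrolled and sets no rule on whose scores are collected or used.

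**Conclusion.** The point holds in a limited form. Followed as written, the primary test excludes anyone missing a visit, including participants whose 4-week primary score is in hand, against an allowance of 12 in 70 (17.1%). For loss of week 16 alone, the illustrated bias at 4 weeks runs from nil to about +0.19 SD (nil to +0.13 SD for the three-visit mean that the named test compares), with type I error at most about 10%. For scale, f = 0.40 with two equal groups corresponds to d = 0.80.

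These sizes depend on an assumed mechanism and are not forecasts. One might also infer that the trial is underpowered or that its result must favour the intervention; neither follows. The change is worth making because a better method is available at little cost.

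**What to change.** Make the primary analysis of each primary outcome a likelihood-based linear mixed model (REML) with baseline as covariate and the arm contrast at 4 weeks. Use every observed follow-up score of every randomised participant, in the arm assigned. Keep multiple imputation as sensitivity analysis.

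State that this analysis is valid under missing at random, and that it does not remove bias from participants with no follow-up score whose loss depends on unseen response. For that reason, also state that planned assessments continue for participants who stop attending sessions. The protocol does not say they would be excluded, so this is a clarification.

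The cost is a change to the analysis wording. No participants and no visits beyond those already scheduled are needed.
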